**Study Protocol**

**(Purpose of the study)**

The purpose of this study is to determine whether topic insulin is effective to accelerate wound healing in diabetic patients.

**(Background of the study)**

An indolent, non-healing wound constitutes a major problem that plagues those with diabetes. Approximately 15% of all patients with diabetes will, at some time, have non-healing wounds, despite insulin treatment and a meticulously-controlled diet, and this is the leading cause of lower extremity amputation. However, the available treatments are awfully expensive or not effective enough.

**(Methods)**

1. The study design

This is a randomized, double-blind, placebo-controlled study. The patients will be recruited in the University Hospital of the State University of Campinas. The trial will be explained to all patients, and their written informed consent will be obtained before any trial-related procedures initiates.

2. Eligibility

Eligible patients are 18 to 80 years-old, both male and female patients with type 1 or type 2 diabetes mellitus with established diagnosis for more than 2 years, and with wounds that were difficult to be healed for at least three months. The probands should also have serum creatinine below 1.5mg/dL.

3. Exclusion criteria

Patients will be excluded if they do not satisfy the inclusion criteria, if the wounds are infected, if cellulites, venous stasis, inadequate perfusion and osteomyelitis are present, and if the patients are unable to attend the follow-up.

4. Informed consent

Patients who are eligible and not excluded according to the exclusion criteria described above will be informed of the background, purpose, method, spontaneous participation, withdraw rights of the study, and gave written consent. Study subjects can read this protocol if necessary.

5. Interventions

Patients who meet the criteria and seen between January 2004 and September 2007 will be considered for the study.

Group I intervention will consist of debridement for the ulcer, administration of the insulin cream (patent number: PI 0705370-3, University of Campinas, Brazil) on the wound, digital photograph by the same observer with the same camera (Sony, Cybershot, 8.1 megapixels) and measurement of the wound (height (↕) x width (↔) weekly, during 8-12 weeks. Group P intervention will consist of debridement for the ulcer, administration of the placebo cream on the wound, digital photograph by the same observer with the same camera (Sony, Cybershot, 8.1 megapixels) and measurement of the wound (height (↕) x width (↔) weekly, during 8-12 weeks.

Blood will be collected in both groups, in order to perform laboratory analysis, such as leukocyte count, hemoglobin, platelet count, glucose, creatinine, and glycosylated hemoglobin. These analyses will be made in the University Hospital of State University of Campinas, in the routine laboratory.

The detailed schedule is shown in the Table 1

Table 1. Schedule of the study

| Visit | Blood Sample | Digital  Photograph | Size of the wound height (↕) x width (↔) | Group I | Group P |
| --- | --- | --- | --- | --- | --- |
| 1 |  |  |  | Active | Placebo |
| 2 |  |  |  | Active | Placebo |
| 3 |  |  |  | Active | Placebo |
| 4 |  |  |  | Active | Placebo |
| 5 |  |  |  | Active | Placebo |
| 6 |  |  |  | Active | Placebo |
| 7 |  |  |  | Active | Placebo |
| 8 |  |  |  | Active | Placebo |

6. Target sample size

Target sample size is 46, which corresponds to the number of patients that attended the inclusion criteria.

7. Administration of the investigatory product (IP)

The insulin or the placebo cream will be administrated according to the schedule table shown in Table 1.

8. Investigatory product

The insulin cream used is prepared with regular insulin (0.5U/g cream) in the pharmacy of our University Hospital and holds the patent number, PI 0705370-3 (University of Campinas, Brazil). In preliminary experiments, we used different concentrations of insulin to prepare the cream, but the doses that induced the best effect in wound healing without changing blood glucose was 0.5U/g. The cream under study, vehicle or with insulin, is applied locally to cover the excision.

9. Randomization

Eligible participants will be provided unique subject identification numbers according to study criteria and will be assigned to the insulin cream group or to the placebo group by a research technician ([name]), according to a computer-generated, randomization plan.

10. Limitation and fixation of concomitant medication

The oral drugs or s.c. insulin used by the patients to treat diabetes will not be changed during the treatment period with placebo cream or insulin cream, that will be at least 8 weeks.

11. Analysis

Primary outcome measure:

% of Wound healing closing measured each week [Time Frame: 7 days ] [ Designated as safety issue: Yes ].

Secondary outcome measure:

Complete wound healing [Time Frame: 8 weeks] [Designated as safety issue: Yes ]

Safety analysis

The prevalence of adverse events will be compared between the insulin and the placebo cream interventions.

12. Statistical analysis

Wound dimensions will be calculated in a blinded fashion and analyzed for homogeneity and significance using the SPSS, version 13.0 (SPSS, Inc., Chicago, IL, USA). All continuous variables will be expressed as means  SE. One-way analysis of variance (ANOVA) will be used to assess the differences in a continuous variable between the two groups of patients. Post hoc analysis was performed using Tukey’s test. All tests will be two tailed, and the level of significance employed will be *P*<0.05.

[Response to adverse events]

In case of adverse events escalation of the investigatory product should be discarded, the investigatory product should be de-escalated or ceased if necessary. Adverse events should be reported to the principal investigator and the study supervisor.

[Handling of study data]

Data will be collected and fixed by the principal investigator. Data will be analyzed after key-open.

[Registration of the study]

The study will be registered in ClinicalTrials.gov.

[Publication of the study]

The study will be published to the journal under the names of the investigators,

or the name of study group if necessary.

ADDENDUM 1.

The form that will be fulfilled in the hospital follows the model below:

Name:_____________________________________________ Number:_____

Birthday date:­­­­­­­­­­­­­­­­___________________________________________________

Gender: □ Male □ Female

□ Type 1 diabetes □Type 2 diabetes Time after the diagnosis:_________

Time of wound:_________________ Wound location:____________________

Wound size:___________________ cm

Signs of infections: □ Yes □ No

Cellulitis: □ Yes □ No

Inadequate perfusion: □ Yes □ No

Osteomyelitis: □ Yes □ No

Beginning of the treatment:__/__/____ □ Insulin Cream □ Placebo

Serum creatinine:________________mg/dL

Weekly evaluation:

__/__/____ Wound size area:_______________cm (height (↕) x weidth(↔))

Aspect of the wound:________________________

Signs of infections: □ Yes □ No

Cellulitis: □ Yes □ No

Inadequate perfusion: □ Yes □ No

Osteomyelitis: □ Yes □ No

Weekly reduction of the wound area: ___________cm (height (↕) x weidth(↔))

Have photographs been taken? □ Yes □ No

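### Section 10 fixes diabetes drugs for the whole cream period with no safety exception, so a medically needed change means breaking the protocol, stopping the cream or withdrawing the patient

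*Combined protocol and SAP*

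**What the plan says.** Section 10 (Limitation and fixation of concomitant medication) states that the oral drugs or s.c. insulin used for diabetes "will not be changed during the treatment period with placebo cream or insulin cream, that will be at least 8 weeks". It names both creams, so it binds both arms. Section 5 has treatment and measurement "weekly, during 8-12 weeks".

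Section 2 admits patients with "type 1 or type 2 diabetes mellitus with established diagnosis for more than 2 years", and Section 10 itself takes it that some use s.c. insulin.

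On the cream, Section 8 describes one strength and reports from preliminary work that "the doses that induced the best effect in wound healing without changing blood glucose was 0.5U/g". Section 7 refers to Table 1, which shows only active or placebo at each visit.

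Under Response to adverse events, escalation is ruled out and "the investigatory product should be de-escalated or ceased if necessary". The same paragraph adds: "Adverse events should be reported to the principal investigator and the study supervisor". It does not mention background diabetes drugs. Section 11 compares adverse-event prevalence between the groups. Section 4 lists the right to withdraw among the matters explained at consent.

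**The concern.** Holding diabetes treatment constant is a sensible aim, because a change in glucose control is a rival explanation for a change in healing. But the rule is absolute. Diabetes patients, especially those on s.c. insulin, may need a dose changed for their own safety during two to three months of treatment. That need can arise in either arm and does not depend on the cream having any effect on glucose.

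If it arises, staff who follow the text have no compliant way to change the dose and keep the patient on trial treatment. At stake are patient safety, if someone puts the rule first, and trial treatment given up without need, if the cream is stopped although it is not the cause. There is also a loss of information: the plan does not require background drug changes or cream stops to be recorded systematically, although Section 10 chose background treatment as something to hold fixed.

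**Working it through.** The point turns on wording, so the check is a side-by-side reading, with arithmetic only for the length of the freeze.

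**1. Is there an exception anywhere?** Sections 5, 7, 8 and 10, Table 1, the adverse-event paragraph and the Addendum 1 form were read for a safety exception, rescue rule or permitted adjustment of diabetes drugs. Number found: 0. Section 5 has glucose and glycosylated haemoglobin measured in both groups, but no section says what may be done about an unsafe value.

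**2. How long does the freeze last?** Section 10 gives a minimum of 8 weeks; Section 5 gives 8 to 12.
- Per patient: 8 × 7 = 56 days to 12 × 7 = 84 days.
- For the target of 46 patients (Section 6), if all complete: 46 × 8 = 368 to 46 × 12 = 552 patient-weeks. Early stops would lower this.

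**3. What can be done as written when a dose needs changing?**

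| Action | Status in the plan |
| --- | --- |
| Acute treatment of low glucose | Not restricted |
| Antibiotics and other non-diabetes medicines | Not restricted |
| Change of oral diabetes drug or s.c. insulin while on cream | Barred by Section 10 |
| Lower step of the cream | None defined: one strength, no stated quantity to reduce |
| Ceasing the cream | Allowed by the adverse-event rule |
| Withdrawal | Allowed by Section 4 |

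The freeze is tied to the period on cream, so the natural reading is that ceasing the cream ends it for that patient. The plan does not say so outright. On that reading, a lasting change of diabetes treatment is open only to a patient who gives up the cream or leaves the trial.

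**4. What is recorded?** The weekly part of the Addendum 1 form covers wound size, its weekly reduction, wound aspect, four local conditions (infection, cellulitis, inadequate perfusion, osteomyelitis) and photographs. It has no field for a diabetes-drug change or a cream stop.

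**5. How many patients might be affected?** The documents give no rate. With an assumed share p of patients needing a change for safety, the expected number is 46p and the chance of at least one is 1 − (1 − p)^46.

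| Assumed p | 46p | 1 − (1 − p)^46 |
| --- | --- | --- |
| 0.01 | 0.46 | 0.370 |
| 0.02 | 0.92 | 0.605 |
| 0.05 | 2.30 | 0.906 |
| 0.10 | 4.60 | 0.992 |

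This table shows only how the count moves with p. It is not evidence that any of these values applies, and the point does not rest on it.

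**The case against.** The strongest reply is that no patient is trapped. Clinicians may treat low glucose at once, the cream can be ceased, and the patient can withdraw. Harm then requires staff to put Section 10 above all of these, which the documents do not ask of them. The freeze also has a legitimate purpose, and Section 8 reports that the chosen strength left blood glucose unchanged.

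Most of this stands and limits the point. What it leaves untouched is the lasting dose change, as opposed to acute treatment: every compliant way to make one costs the patient the cream or the trial. Section 8's finding on the cream does not help, since the freeze binds the placebo arm equally and the need can come from the background drugs themselves.

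Several stronger readings are tempting, and the documents do not support them:
- *That ceasing the cream is the only treatment change possible.* The freeze covers diabetes drugs alone; other medicines and acute care are open, and so is withdrawal.
- *That the adverse-event rule cannot work.* It offers ceasing as an alternative, and ceasing is clear enough to carry out. The reference to escalation is redundant in a plan that has none, but harmless. Less cream or fewer applications are undefined, not forbidden.
- *That drug changes and cream stops could not be reported by arm.* The form is a model that lacks a dedicated field. Adverse events are reported separately and compared by group. What is missing is a requirement to record these changes systematically.

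**Conclusion.** The point holds in a limited form. Section 10 states an absolute rule with 0 safety exceptions, lasting 56 to 84 days per patient in both arms. Followed literally, it leaves an unsafe diabetes-drug dose in place unless the protocol is broken, the cream is stopped or the patient withdraws. This rests on the literal wording and on reading the freeze as ending with the cream.

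The undefined de-escalation is a drafting matter that would not merit a point on its own. A reader might infer from the gap a bias in the treatment comparison or a loss of power. Neither is shown: the rule is the same in both arms, and the frequency of such events is not in the documents. It is a patient-safety and record-keeping improvement that should be made because it is specific and cheap. It does not threaten the validity of the trial.

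**What to change.** **Section 10.** Add after the freeze: 'except when needed for patient safety (for example low glucose), with the date, reason and change recorded, in either arm and without breaking the blind'.

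**Addendum 1.** Add one field to the weekly evaluation for changes in background diabetes drugs and for cream stops. Report both by arm beside the adverse-event comparison in Section 11.

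**Response to adverse events.** Replace 'de-escalated or ceased' with 'suspended or ceased', since only one strength is defined. Keep the sentence on reporting to the principal investigator and study supervisor.

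**Cost.** A clause, a word and a form field, with no extra visits, tests or patients. The downside is that a few permitted drug changes may slightly affect glucose control and so healing. They would be allowed on the same terms in both blinded arms, and the record by arm would let a reader see whether they differ.

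### The weekly primary outcome has no named primary week, summary measure or multiplicity rule, so the 5% level is secured only if a single comparison is fixed in advance

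*Combined protocol and SAP*

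**What the plan says.** Section 11 (Analysis) gives the primary outcome as percent "of Wound healing closing measured each week [Time Frame: 7 days". Section 5 (Interventions) has the wound photographed and measured "weekly, during 8-12 weeks", and Table 1 lists eight visits. Section 10 describes a treatment period "that will be at least 8 weeks". The secondary outcome, complete healing, has an 8-week time frame.

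Section 12 (Statistical analysis) states: "One-way analysis of variance (ANOVA) will be used to assess the differences in a continuous variable between the two groups of patients". It continues: "Post hoc analysis was performed using Tukey’s test". On the error level it says "All tests will be two tailed, and the level of significance employed will be" P<0.05. Nothing in the document names a primary week, a summary over weeks, a model for repeated measurements or an adjustment for several tests. Addendum 1 has a field for the weekly reduction in wound area at each weekly evaluation. Under the data-handling heading, analysis takes place after the treatment code is opened.

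**The concern.** Each patient contributes several correlated values of the primary outcome, but the planned test takes one value per patient. The analyst must therefore choose a single week, test every week, or put all weeks into one analysis. These choices have different error rates, and the plan does not choose. Since analysis follows unblinding, nothing in the text prevents the deciding week from being picked after the group results are seen.

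The 7-day time frame does not settle the matter. It could mean a single comparison at week 1, the interval between measurements, or a weekly rate of closure.

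At stake is the trial's main inference. Without a named comparison, a difference significant in one week cannot be told apart from the best of several chances.

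**Working it through.** **Inputs from the protocol.** Weekly measurement for 8 to 12 weeks (section 5); eight visits (Table 1); 46 patients in total (section 6); two groups, one-way ANOVA, every test at two-sided 0.05 (section 12). If visit 1 is the baseline, percent closure there is zero by definition, so there are 7 looks rather than 8, or 11 rather than 12.

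**Assumptions, not in the protocol.** Equal allocation, 23 per arm (no ratio is stated); complete data at every look; the within-patient correlation, varied from independence to 0.95.

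**Step 1: the stated level.** For one test, 1 − 0.95 = 0.05. Two-group ANOVA is the two-sample t test; in simulated null trials its rate at a single week was 4.8% to 5.2%. The 5% is correct per test. The plan states no overall rate.

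**Step 2: Tukey.** With two groups there is one contrast, and the studentized range statistic is q = √2·|t|. The P value is therefore the ANOVA P value, with no adjustment over weeks.

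**Step 3: every week tested, any significant week counted.** For k independent tests the rate is 1 − 0.95^k. Correlated cases come from 40,000 simulated null trials each.

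| Assumed correlation | 7 looks | 8 looks | 11 looks | 12 looks |
|---|---|---|---|---|
| Independent (formula) | 30.2% | 33.7% | 43.1% | 46.0% |
| Exchangeable 0.5 | 23.5% | 25.2% | 30.9% | 32.6% |
| Exchangeable 0.8 | 14.8% | 16.1% | 18.1% | 19.0% |
| Exchangeable 0.95 | 9.2% | 10.0% | 10.4% | 10.7% |
| AR(1) 0.9 | 14.9% | 16.3% | 20.3% | 21.8% |
| Cumulative random walk | 17.1% | 18.1% | 20.7% | 20.9% |

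Independence is close to an upper limit, because weekly areas in one patient should be positively correlated.

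**Step 4: all weeks pooled as independent values.** The text does not state this; it is shown because it is the other way to put all the weekly data through the stated test. Eight weeks give 8 × 46 = 368 values. The variance of a group mean is understated by a factor D, so the rate is about 2[1 − Φ(1.96/√D)].

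- AR(1) 0.6: D = 1 + 2Σ(1 − j/8)·0.6^j, summed over j = 1 to 7, = 3.08. 1.96/√3.08 = 1.12, giving about 26%.
- Exchangeable 0.9: D = 1 + 7 × 0.9 = 7.3. 1.96/√7.3 = 0.73, giving about 47%.

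Simulation over exchangeable 0.5 to 0.9 and AR(1) 0.6 to 0.9 gave 26.4% to 47.6%. A repeat with more runs reached 48.1%. Here higher correlation makes matters worse, the reverse of step 3.

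**Step 5: one named test against adjusting for all weeks.** The detectable difference at 80% power is (z for alpha + 0.842) × √(2/23), where √(2/23) = 0.295.

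- One test at 0.05: (1.960 + 0.842) × 0.295 = 0.83 SD.
- Bonferroni over 8 looks (0.05/8 = 0.00625): 1.05 SD.
- Bonferroni over 12 looks (0.05/12 = 0.00417): 1.09 SD.

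**The case against.** A reader might infer that the trial's real false-positive rate is several times 5%. The documents do not support that as a fact. They do not say that ANOVA is run separately each week, that any one significant week makes the trial positive, or that patient-weeks are pooled. Section 12 speaks of a continuous variable compared between two groups, which also fits one value per patient tested once, at exactly 5%. The 7-day time frame could be read as just that, a single week-1 comparison, and the weekly-reduction field in Addendum 1 makes a rate of closure another possible reading.

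The size is also uncertain. The correlations and the 1:1 split are assumptions, and at exchangeable 0.95 the inflation is only about twofold. Twelve looks is the outer limit, since Table 1 has eight visits and only a minimum treatment period is fixed.

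All of this stands, and it makes the error rates conditional. It does not remove the gap. A single week-1 test sits badly with an outcome measured every week, since it would leave all later weeks out of the primary outcome. That several readings are possible, with error rates from 5% to over 40%, is the defect.

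It is also fair to say that the planned ANOVA at one named week would hold 5% without adjustment for baseline area. Naming one week is what secures the error rate; the form of the model is a further choice.

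**Conclusion.** The concern holds in conditional form. The plan does not identify the primary comparison for a weekly outcome, and nothing in it controls error across weeks. If each week is tested and any significant week counts, the false-positive chance is about 9% to 34% for 7 or 8 looks and up to about 46% for 12, roughly 2 to 9 times 5%. If eight weeks were pooled as independent values, it would be about 26% to 48% at the correlations tried. If only one week named in advance is tested, it is 5%.

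That the primary comparison is missing is certain from the text. The size is less certain: it rests on 23 per arm, complete data and correlations that the protocol does not give.

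**What to change.** In sections 11 and 12, name one primary test: the between-group difference in percent reduction in wound area from baseline at week 8, by one ANCOVA adjusted for baseline area, at two-sided 0.05. Week 8 is already the secondary outcome's time frame and lies within the minimum treatment period. Give only this one model as primary, so that two candidate analyses do not replace the present ambiguity.

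Replace the 7-day time frame with week 8, and state which visit is baseline. If visit 1 is baseline and visits are weekly, visit 8 falls seven weeks later, so Table 1 and section 5 must be reconciled on which assessment is week 8. Report the other weeks as estimates with 95% confidence intervals and no significance claims. Delete the Tukey step.

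The cost is that significance claims at other single weeks are given up and the timing of the primary outcome is fixed. In return, the detectable difference stays at 0.83 SD rather than the 1.05 SD that Bonferroni over eight looks would require (80% power, 23 per arm assumed).

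### The plan promises a between-arm adverse-event comparison, but the only form shown prompts for local wound complications alone, so systemic events, including hypoglycaemia, would go unsolicited

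*Combined protocol and SAP*

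**What the plan says.** Section 11, under the safety analysis, makes one commitment: "The prevalence of adverse events will be compared between the insulin and the placebo cream interventions". It does not define an adverse event or say how events are to be elicited.

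Addendum 1 opens with "The form that will be fulfilled in the hospital follows the model below". Its weekly block has a date, wound size, a free-text line "Aspect of the wound", yes/no boxes for "Signs of infections", cellulitis, inadequate perfusion and osteomyelitis, the weekly area reduction and a photograph check. The only laboratory value anywhere on the form is "Serum creatinine", entered once in the entry part.

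Section 5 says "Blood will be collected in both groups, in order to perform laboratory analysis", and glucose and glycosylated hemoglobin are among the tests it lists. Section 8 reports that the concentration giving the best healing effect "without changing blood glucose was 0.5U/g". The paragraph on the response to adverse events directs reports to the principal investigator and the study supervisor, without giving a record format. Section 12 specifies ANOVA for continuous variables and names no method for proportions.

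**The concern.** To compare prevalence between arms, every patient must be asked the same question at the same intervals. Addendum 1 does this for four wound complications and for nothing else.

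The product contains insulin, and under Section 10 patients keep their existing oral drugs or subcutaneous insulin unchanged. Section 8 itself treats unchanged blood glucose as part of the reason for the chosen concentration. Systemic glucose effects are therefore a safety question the plan has raised, yet the form does not ask about them. If the form is used as shown, a report of no hypoglycaemia in the insulin arm could not be told apart from a failure to ask. No later analysis can recover events that were never recorded.

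**Working it through.** There is no figure in the plan to reproduce. Section 6 gives a total of 46 with no event rate, effect size or power. The check is a comparison of texts, followed by an illustration on stated assumptions.

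**Step 1: what the form can supply.**
- Local wound complications: four yes/no items, repeated weekly, in both arms. Comparable.
- Wound appearance: free text, weekly. Usable as supporting information.
- Any other adverse event (type, date, severity): no field.
- Hypoglycaemia: no field.
- Glucose and glycosylated hemoglobin: measured under Section 5, but no field on the form and no mention in the safety analysis.

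**Step 2: other routes into the data.** Events reported to the principal investigator reach the person who, under the handling of study data, collects and fixes the dataset. That is a route, but the documents describe no prompting question, grading or record to go with it.

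**Step 3: the analysis.** Adverse-event prevalence is a proportion. Section 12 names a test for continuous variables only, so the promised comparison has no stated method.

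**Step 4: illustration.** Assumptions that are not in the documents: 1:1 allocation, so 46/2 = 23 per arm; true rate p; each affected patient recorded independently with probability s.

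The chance of at least one recorded event in an arm is 1 − (1 − p·s)^23. With p = 10%:
- s = 1: p·s = 10%, chance 91%, so zero recorded in 9%.
- s = 0.5: p·s = 5%, chance 69%, so zero recorded in 31%.
- s = 0.2: p·s = 2%, chance 37%, so zero recorded in 63%.

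Power of Fisher's exact test, two-sided 0.05, for assumed true rates of 10% and 50%, with the same s in both arms:
- s = 1 (10% v 50% recorded): 81%.
- s = 0.75 (7.5% v 37.5%): 62%.
- s = 0.5 (5% v 25%): 37%.
- s = 0.25 (2.5% v 12.5%): 9%.

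The one-sided 95% upper bound for zero events in 23 is 1 − 0.05^(1/23) = 12.2%. This assumes complete capture and describes the sample size, not the gap in the form. Even with every event recorded, Fisher power for 5% against 20% is only 22%.

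**The case against.** The strongest reply is that the plan does collect safety data. For a cream applied to a wound, infection, cellulitis, poor perfusion and osteomyelitis are plausible harms, and all four are asked weekly on the same form in both arms. Glucose is planned in both groups through the routine laboratory. Addendum 1 is described as a model, so other records may exist. Reported events do reach the principal investigator. All of this stands, and it limits the point to systemic and other general events. It does not supply a prompted question about them.

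A reader might infer more than the documents support:
- **That no safety comparison is possible.** The four weekly items can be compared between arms, and bounds can be put on them.
- **That Addendum 1 is the only data form.** It is the only form shown.
- **That glucose is missing from the plan.** It is missing from the form; Section 5 plans the measurement.
- **That the 12.2% bound measures this defect.** It would apply with perfect recording, and the 23 per arm is itself assumed because no allocation ratio is given.
- **That patients with venous stasis could be enrolled because the form has no box for it.** Section 3 excludes patients "if cellulites, venous stasis, inadequate perfusion and osteomyelitis are present", and the form is not described as the screening tool. This is a separate eligibility matter with no bearing on adverse-event prevalence.
- **That glucose change can be analysed at no extra cost.** That needs a post-baseline sample. The cells of Table 1 are blank in the available text, possibly because marks were lost, so the timing of blood samples cannot be judged.

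**Conclusion.** The point holds for systemic and general adverse events, including hypoglycaemia. The form shown does not ask about them, no other systematic means of collection is described, and no test is named for the comparison that Section 11 promises. It does not hold for the four local wound complications.

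The loss cannot be sized from the documents, since it depends on an unknown share of events reported unprompted. On the assumed figures above, recording half the events raises the chance of an apparently event-free arm from 9% to 31% at a true rate of 10%, and cuts Fisher power for 10% against 50% from 81% to 37%. The rates, the capture shares and 23 per arm are all assumptions.

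The change should be made, because it alters which data are collected and cannot be made good at analysis.

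**What to change.** 1. Add to each weekly block of Addendum 1, worded identically in both arms: *Adverse event since last visit: Yes/No (type, date, severity)* and *Hypoglycaemia since last visit: Yes/No*.
2. Add fields to transcribe the glucose and glycosylated hemoglobin results that Section 5 already plans.
3. In Sections 11 and 12, state that the proportion of patients with at least one event will be compared by arm with Fisher's exact test and a confidence interval for the difference. The interval matters because 46 patients cannot exclude moderate differences.
4. If Table 1 schedules a post-baseline blood sample, compare glucose between arms adjusted for baseline glucose. If it does not, say that no such comparison will be made.

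The cost is a few lines on the form, a few sentences in the plan and slightly longer visits. Whether the glucose comparison would need further sampling depends on Table 1.

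### The only between-group test named is an unadjusted one-way ANOVA; adjusting percent closure for baseline wound area would cost almost nothing and could gain precision

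*Combined protocol and SAP*

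**What the plan says.** Section 12 (Statistical analysis) gives one comparison method for continuous data: "One-way analysis of variance (ANOVA) will be used to assess the differences in a continuous variable between the two groups of patients". It adds a Tukey post hoc test, which has no further pairs to compare when there are two groups. It also sets the significance rule, "All tests will be two tailed, and the level of significance employed will be" P<0.05. No covariate, repeated-measures model or confidence interval is mentioned. Wound dimensions are to be analysed for homogeneity, but the section does not say what that means or what would follow from it. For summaries, "All continuous variables will be expressed as means" with SE.

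Section 11 defines the primary outcome as the percentage "of Wound healing closing measured each week", with "Time Frame: 7 days" as the time frame. It does not say whether the reference area is the baseline area or the previous week's.

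Section 6 says "Target sample size is 46, which corresponds to the number of patients that attended the inclusion criteria". No effect size, SD or power is given. Section 9 refers to a computer-generated plan, without an allocation ratio or stratification factor.

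The form in Addendum 1 has fields for wound size and for how long the wound has been present. Both stand in its opening part, ahead of the weekly evaluations. Section 2 requires a wound of at least three months' standing but sets no upper limit on duration and no limits on area.

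**The concern.** With two groups, one-way ANOVA is the two-sample t-test. It compares mean percent closure and leaves all variation linked to initial wound size in the error term. Entry is open to wounds of any area, so baseline areas may vary widely.

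Percent closure could depend on initial area even after division by it. For example, if wound edges advance at similar absolute rates, small wounds close by a larger percentage in a given week than large ones. This is a possibility, not something the documents report.

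If it is so, two things are at stake in a trial of 46:

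- Residual variance that a recorded covariate could remove stays in the comparison.
- Any baseline difference that occurs between the arms shifts the estimated treatment effect, with no planned correction.

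**Working it through.** **The plan's own figure.** The target of 46 cannot be reproduced, because no effect, SD or power is stated. Solving backwards with 23 per arm, two-sided 0.05 and the normal approximation, the difference detectable with 80% power is (1.960 + 0.842) × √(2/23) = 0.826 SD.

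**Inputs**

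- From the documents: total 46 (section 6); two-sided 5% level (section 12).
- Assumed: 1:1 allocation (23 per arm), no dropout, roughly normal outcomes, a true effect of 0.6 SD, and a correlation ρ between the covariate and percent closure from 0 to 0.6. With two covariates, ρ is their joint (multiple) correlation with the outcome.

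**Chance imbalance.** The SE of the standardised baseline difference is √(2/23) = 0.295.

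- P(|difference| > 0.3 SD): 0.3/0.295 = 1.017, so 31%.
- P(|difference| > 0.5 SD): 0.5/0.295 = 1.696, so 9%.

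**What an imbalance does.** An imbalance of b SD shifts the unadjusted effect by ρb. Given b = 0.5, the test statistic under the null has mean ρ × 0.5/0.295 and SD √(1 − ρ²).

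- ρ = 0.3: shift 0.15 SD, conditional type I error 6.9%.
- ρ = 0.5: shift 0.25 SD, conditional type I error 10.0%.

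Averaged over all randomisations the rate is 5%.

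**Power.** With k covariates, the variance of the treatment difference is (2/23)(1 − ρ²) × c. The factor c is the average cost of estimating the covariate effects: 1 for none, 1 + 1/42 = 1.024 for one, 1 + 2/41 = 1.049 for two. Degrees of freedom are 44, 43 and 42. Power comes from the noncentral t with noncentrality 0.6/√variance. For the unadjusted test this is 0.6/0.295 = 2.035, which gives 51.2%.

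| ρ | Unadjusted | One covariate | Two covariates |
|---|---|---|---|
| 0 | 51.2% | 50.2% | 49.3% |
| 0.2 | 51.2% | 51.9% | 50.9% |
| 0.3 | 51.2% | 54.0% | 53.0% |
| 0.5 | 51.2% | 62.2% | 61.1% |
| 0.6 | 51.2% | 69.0% | 68.0% |

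**Break-even.** Adjustment pays once (1 − ρ²) × c falls below 1. That gives ρ = √(1 − 1/1.024) ≈ 0.15 for one covariate and √(1 − 1/1.049) ≈ 0.22 for two. Within the range, the worst loss is 51.2 − 50.2 = 1.0 point (one covariate) or 51.2 − 49.3 = 1.9 points (two). The largest gain is 69.0 − 51.2 = 17.8 or 68.0 − 51.2 = 16.8 points.

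**The case against.** The strongest reply is that nothing is broken. Unadjusted ANOVA in a randomised trial is valid, and its standard error already allows for chance baseline differences. A reader might infer that the plan raises the false-positive rate. It does not: the higher rates above apply only given an imbalance of that size, and they average out to 5%. Lost precision and exposure to imbalance are also largely one cost seen from two sides, so they should not be added together. This stands.

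A reader might also infer that the plan ignores baseline area altogether. That goes too far. Percent closure has an earlier area as its denominator, and if that area is baseline, initial size already enters the outcome. Dividing by baseline does not, however, remove a remaining dependence of percent closure on initial size, so a narrower point survives.

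A third tempting inference is that a substantial loss of power has been shown. The documents give no correlation, SD or expected effect, so they do not support that. Below the break-even correlation, adjustment gains nothing.

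Finally, section 12 does not label ANOVA as the primary test. It governs the primary outcome only because no other between-group method is named. The undertaking to analyse dimensions for homogeneity is not a substitute: no consequence is attached to it, and a baseline check without prespecified adjustment does not alter the estimate.

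**Conclusion.** The point holds as an efficiency recommendation about a valid test. The default primary comparison is unadjusted, the covariate is already recorded, and no stratification by wound size is stated.

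The size of the benefit depends on a correlation that the documents do not give. At 0.6 SD, power moves from 51% to between 50% and 69% with one covariate, or between 49% and 68% with two, over ρ from 0 to 0.6. The balance is lopsided in favour of adjusting: about 1–2 points lost at worst, against up to about 18 gained. These figures rest on 1:1 allocation, complete follow-up and near-normal outcomes.

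The change should be made, more so because 46 has no stated power basis. Confidence is high that the test is unadjusted and low on how much adjustment would gain.

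**What to change.** In section 11, define percent closure relative to baseline area and name one primary time point. ANCOVA cannot be carried out as a primary analysis until both are fixed.

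In section 12, replace one-way ANOVA for percent closure with ANCOVA on treatment plus log baseline area. Wound duration may be added as a second covariate; decide this before the key is opened. Report the adjusted between-group difference with its 95% CI. Add a rank-based ANCOVA as a sensitivity analysis, because percent closure is capped at 100 and has no lower bound.

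The cost is wording, one or two degrees of freedom, and about 1–2 points of power if the covariates turn out not to be prognostic. No new data are needed.

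A separate presentation point does not affect the test: describe patients by SD, or by median and IQR, instead of SE. At 23 per arm the SE is SD/√23 = SD/4.8, which makes patients look far more alike than they are.
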